***Pilot trial***: We conducted a pilot trial to examine the effects of HIAT on plasma biomarkers that have been implicated in the pathophysiology of primary dysmenorrhea. The pilot trial findings indicated a trend towards increased progesterone levels (***d*** = 0.36) and decreased levels of prostaglandin F2 alpha (PGF2α) metabolites (***d*** = 0.35) in the HIAT group compared with those in the control group, which suggested that aerobic exercise may affect primary dysmenorrhea pain through effects on these mediators.^8, 13^

Because our research has supported the beneficial effects of HIAT, and a recent pilot study suggested a link between HIAT and progesterone and prostaglandin levels, the proposed randomised, controlled cross-over trial will test the following three hypotheses: (1) HIAT for 12 weeks will lead to significant reductions in pain intensity and absenteeism and improve academic performance compared to baseline levels; (2) pain improvements will be mediated by increased progesterone levels, resulting in decreased PGF2α levels; (3) HIAT will display superior cost-effectiveness compared with usual care (Wait-list control [WLC]) for primary dysmenorrhea treatment.

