***Research design and recruitment.*** A mixed-methods study, including a cross-over RCT, and semi-structured focus groups, alongside economic evaluation, will be conducted. A Cross-over design will be adopted to minimize the effect of confounders and inter-individual variability (because each participant serves as their own control)^27^ and encourage participant enrolment in the trial.^28^ A mixed-methods approach will be considered because the combination of qualitative and quantitative methods can contribute to interdisciplinary and comprehensive research evidence.^29^ This trial will include: (1) a two-step screening phase for eligibility; (2) a baseline assessment (time-point [T1]); (3) 12 weeks of supervised treadmill training for the HIAT group; (4) post-treatment outcome assessments and economic evaluations at 12 weeks (T2); (5) a washout period for four weeks, followed by the cross-over of HIAT and WLC groups; (6) 12 weeks of supervised treadmill training for the WLC group; (7) outcome assessments at 28 weeks (T3); and (8) semi-structured focus groups at 32 weeks. Potential participants will be recruited via advertisements (study flyer) distributed at the Hong Kong Polytechnic University and the Education University of Hong Kong (please see upport letter) campuses and throughout the local community and by word-of-mouth.

***Sample size:*** G-Power analysis^30^ (3.1.9.2), set for an F-test (analysis of variance (ANOVA), was used to estimate the sample size required to reliably test the study hypotheses. We will enrol 130 participants (65 per group), allowing for a 30% attrition rate (the drop-out rate in our previous RCT^9^ with a seven-month follow-up was 20%–23%). For Hypothesis 1, the estimated sample size was 86 (43 per group). The power was set to 90%, the alpha level was 0.05, the drop-out rate was 30%, and effect-size was 0.60 (from our previous RCT^9^). For Hypothesis 2, based on estimated changes in progesterone levels from our pilot trial (***d*** = 0.36),^13^ the sample size required to detect differences in progesterone with 90% power at the 5% significance level is 100 (50 per group). Assuming a 30% drop-out rate, 130 participants (65 per group) would be required.

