***Hypothesis 2.*** The mediation effects of increased progesterone levels on pain will be assessed using the Sobel test.^51^ A four-step model using linear regression will be tested. In Step 1, the regression coefficient between prostaglandin levels and pain (Path C) will be estimated. In Step 2, the regression coefficient between progesterone and prostaglandin levels (Path A) will be estimated. In Step 3, the regression coefficient between pain and prostaglandin levels, along with the mediator, progesterone levels (Path B), will be evaluated. Step 4: the Sobel test will be used to estimate the standard error of Path AB using the formula B^2^SA^2^ + A^2^SB^2^, where A and B are the regression coefficients of Paths A and B, respectively, and SA and SB are the standard errors of Paths A and B, respectively.^51^ The online Sobel test calculator (<http://quantpsy.org/sobel/sobel.htm>) will be used. Hypothesis 2 will be supported if the Sobel test indicates a significant (p < 0.05) mediation effect.

***Hypothesis 3***. The unadjusted mean costs and cost differences between HIAT and the usual care groups for total and disaggregated costs (intervention costs, healthcare utilisation costs, including healthcare services and medications utilised, and absenteeism costs) will be calculated.^48^ The seemingly unrelated regression (SUR) analyses will be used to estimate the total cost differences (ΔC) and effect differences (ΔE). The SUR analyses will be performed by adjusting for baseline demographic and health characteristics (such as pain intensity and menstrual-cycle length or the number of bleeding days) between groups.^48, 52^ The advantage of SUR is that two regression equations, one for ΔC and one for ΔE, are modelled simultaneously allowing possible correlations between cost and outcome differences to be accounted for.^48, 53^

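### The 90% power stated for Hypothesis 2 belongs to an ANOVA test of a progesterone difference, not to the Sobel test that alone decides the hypothesis

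*Protocol*

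**What the plan says.** The Sample size paragraph states that a G*Power calculation, set for an ANOVA F-test, "was used to estimate the sample size required to reliably test the study hypotheses". For Hypothesis 2 the input is the pilot progesterone effect, d = 0.36. The pilot description in the background shows this to be a between-group contrast: progesterone "in the HIAT group compared with those in the control group". From it the protocol concludes that "the sample size required to detect differences in progesterone with 90% power at the 5% significance level is 100 (50 per group") and then: "Assuming a 30% drop-out rate, 130 participants (65 per group) would be required". Hypothesis 1 is given a smaller requirement (86), so Hypothesis 2 sets the enrolled number.

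Hypothesis 2 itself is a mediation claim: "pain improvements will be mediated by increased progesterone levels, resulting in decreased PGF2α levels". Under Statistical tests and anticipated results, Hypothesis 2, it is analysed by linear regressions. Path A is the progesterone-prostaglandin coefficient. Path B comes from the regression of pain on prostaglandin with progesterone as the mediator. Treatment group appears in none of these regressions. The only decision rule is: "Hypothesis 2 will be supported if the Sobel test indicates a significant (p < 0.05) mediation effect".

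**The concern.** The sizing and the decision rule concern different quantities. The sizing is for a difference in mean progesterone, whereas the decision rests on a product of two regression coefficients, A × B. Nowhere does the protocol assume a size for A, B or their product, and it gives no power for the Sobel test. Yet the calculation is offered as sufficient to test the study hypotheses reliably, and it fixes the enrolment.

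Identifying the mechanism is one of the three stated next steps of the research programme. A reader who sees a non-significant Sobel test beside a 90% power statement could give that result more weight than the design supports.

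**Working it through.** **Inputs from the protocol.** d = 0.36; alpha 0.05 (taken as two-sided); 90% power; 100 participants, 50 per group; 130 enrolled; 30% drop-out. Completers: 130 × 0.70 = 91.

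**Inputs not in the protocol (assumptions).** The sizes of paths A and B; one independent record per participant; B read as the coefficient of the mediator in the pain regression.

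**Step 1. The plan's own figure.** In a plain two-group comparison the requirement is 2 × (1.960 + 1.282)² / 0.36² = 162.2, so 163 per group rather than 50. With 50 per group the expected z is 0.36 × √(50/2) = 1.80, and power is Φ(1.80 − 1.96) ≈ 0.44 (0.43 by the noncentral t).

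A total of 100 can be recovered from a repeated-measures group-by-time F-test with f = 0.36/2 = 0.18. Two measurements with correlation 0.4 give 90.2% power at N = 100, and three measurements with correlation 0.25 give 90.3%. Neither correlation is in the protocol, so the routine actually used cannot be identified.

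**Step 2. Relation of the Sobel test to path A.** With z = AB / √(B²SA² + A²SB²), dividing through by AB gives

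|z| = 1 / √(1/zA² + 1/zB²).

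This is smaller than |zA| for any finite zB. If path A is HIAT to progesterone, Sobel power cannot reach the power for the progesterone difference.

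**Step 3. Treatment as exposure, path A granted 90% at N = 100.** Then zA = 1.960 + 1.282 = 3.24. For a path B partial correlation r, zB = r/√(1 − r²) × √(N − 3). At r = 0.3 and N = 100, zB = 3.10, and putting the expected values into the formula gives 1/√(1/3.24² + 1/3.10²) = 2.24, against 3.24 for path A alone. At 91 completers path A must be scaled too: 3.24 × √0.91 = 3.09. Drawing zA and zB as normal variables with unit variance and counting |z| > 1.96 gives:

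| Path B r | Sobel, N = 100 | Sobel, N = 91 | Sobel, N = 100, zA = 1.80 (plain two-group, d = 0.36) |
|---|---|---|---|
| 0.2 | 27% | 23% | 7% |
| 0.3 | 60% | 52% | 20% |
| 0.4 | 81% | 75% | 32% |
| 0.5 | 87% | 83% | 38% |

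**Step 4. The regressions as written.** Exposure prostaglandin, mediator progesterone, outcome pain. Here d = 0.36 enters nowhere. Simulated datasets with both paths equal give the following, where each range covers path B as a standardised slope or as a partial correlation:

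| Both paths | N = 100 | N = 91 |
|---|---|---|
| 0.2 | about 10% | about 8% |
| 0.3 | 53%-57% | 45%-50% |
| 0.4 | 92%-95% | 88%-92% |

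**Step 5. What another test would gain.** The joint-significance test requires both paths to be significant. Under the Step 3 assumptions at r = 0.3 and N = 100, its power is 0.90 × Φ(3.10 − 1.96) = 0.90 × 0.87 ≈ 79%, against 60% for Sobel. At 91 completers zB = 2.95, and power is Φ(3.09 − 1.96) × Φ(2.95 − 1.96) = 0.87 × 0.84 ≈ 73%, against 52%.

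**The case against.** The strongest reply is that the protocol words the 90% as power for a progesterone difference, so read literally it never claims 90% for the Sobel test. That is fair to the sentence but not to the paragraph, which presents the calculation as the one needed to test the hypotheses and labels this part of it Hypothesis 2. Nor can the point be left to a statistical analysis plan, because the protocol itself fixes both the sizing and the decision rule.

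Three objections to going further do stand.

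- A reader might infer that the trial is certainly underpowered for mediation, or that a true mediation would be missed 40%-50% of the time. The documents do not support this. That miss rate belongs to correlations near 0.3 only. In the regressions as written, two paths of 0.4 bring power above 90% at N = 100, and larger paths raise it further.
- A reader might infer that the 90% is at least correct for the HIAT-control progesterone comparison. The stated inputs do not deliver that either: a plain two-group comparison gives about 43%, and 90% returns only with a correlation that the protocol does not state.
- The protocol says when Hypothesis 2 is supported, not how a null result will be read. The risk of over-interpretation is a reasonable worry, not something the document commits to.

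The simulations also treat each participant as one record. The protocol does not say which time-points or change scores enter the regressions, so the figures show scale rather than exact power.

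**Conclusion.** The point holds. The 90% was computed for a different test and does not apply to the one that decides Hypothesis 2. This conclusion needs no assumption, since it follows from setting the sizing paragraph beside the decision rule.

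Its size does rest on assumptions. With treatment as the exposure and path A granted 90% at N = 100, the shortfall against 90% is about 63, 30, 9 and 3 percentage points for path B correlations of 0.2, 0.3, 0.4 and 0.5, and power stays below 90% however large path B is. If path A has only the strength of d = 0.36 in a plain two-group comparison, Sobel power is about 7%-38%. In the regressions as written both paths are unspecified, and power may fall well below 90% or exceed it. Underpowering is likely for modest paths but is not established.

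**What to change.** **Sample size paragraph.** Remove the implication that 90% power applies to Hypothesis 2. Say that the calculation concerned a progesterone difference only, and restate that power with the G*Power routine and correlation actually used. Simply relabelling the 90% as power for the HIAT-control comparison is not enough, given the 43% from a plain two-group calculation.

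**Statistical tests, Hypothesis 2.** Define the indirect effect with treatment as the exposure: HIAT to progesterone, and on to PGF2α and pain. Replace the Sobel test with a bootstrap confidence interval for that effect (the protocol already plans 5,000 bootstrap replications for the cost analysis) or with a joint-significance test of the paths. State the power of the chosen test at about 91 completers over a range of sizes for both paths, not path B alone.

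**Cost.** Rewording in two places, a short simulation and a few lines of analysis code. Enrolment stays at 130. The downside is that the stated power for Hypothesis 2 becomes less favourable.

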***Procedure:*** Potential participants will undergo a two-step screening process. The first step will be conducted via telephone interview, using an eligibility checklist. Potentially eligible women will then be invited to an in-person screening session on the first day of their next menstrual period. During this session, women will complete the screening questionnaire and IPAQ to determine eligibility, assess baseline physical-activity levels, and obtain written informed consent and anthropometric measurements. Baseline assessments of primary and secondary outcomes and the costs and absenteeism data associated with each individual’s previous three menstrual cycles will be performed, and saliva samples will be collected. Participants will then be randomised into HIAT or WLC groups. Participants in the HIAT group will receive supervised treadmill training for the first 12 weeks of the trial. To minimise carryover effects, a four-week washout period will be observed for all study participants before cross-over. During the washout period, the HIAT group will discontinue exercise, and both groups will continue to manage pain as usual (i.e. with analgesics). After the four-week washout period, the cross-over period will begin during Week 16, and the participants initially randomised to the WLC group will receive the HIAT regimen from Weeks 14–28. Participants initially randomized to HIAT group will be instructed not to engage in exercise during the remainder of the study period (i.e. Weeks 14-28). Participants will be permitted to use analgesics for menstrual pain as needed throughout the study and will be instructed to record the dose and number of pills consumed in an electronic diary. As a diagnosis of primary dysmenorrhea can be confirmed by collecting detailed history;^33, 34^ a pelvic examination/ ultrasound will not be conducted.

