***Intervention.*** The exercise intervention will last for 24 weeks (12 weeks for the HIAT group and 12 weeks for the WLC group) at PolyU. Supervised treadmill (Zebris FDM-T) training at PolyU will begin on the first day of the second menstrual period (baseline assessments will be completed during the first menstrual period). Exercise sessions at PolyU will be instructed and supervised by a registered physiotherapist (RPg student). Using this supervisory method, the participant-to-research person ratio will be 1:1. The rationale for providing supervised sessions is to increase adherence to study interventions because, in our previous RCT^9^, adherence was higher for supervised sessions than for unsupervised home exercise sessions. MHR will be calculated using the conventional age-predicted formula (220 – age). To achieve the target HR, the speed of the treadmill will be gradually increased, based on the participants’ HR, which will be displayed on the treadmill, and the rating of perceived exertion (RPE). Because the current proposed study does not involve graded, incremental exercise, graded-exercise testing (such as VO_2max_ evaluation) will not be performed.

*HIAT.* Women will perform treadmill-based aerobic exercise for three days a week, at 70%–85% of MHR for 30 minutes and perceived exertion of 14–16, based on the Borg RPE scale. This range^39^ is considered to represent HIAT. Aerobic training will be preceded by warm-up exercises for 10 minutes and followed by cool-down exercises for 10 minutes, at a perceived exertion of 11.0 (Borg RPE). These exercise parameters are based on our previous studies^9,10^ and the American College of Sports Medicine guidelines.^40^

*WLC*. Women in the WLC group will be instructed to continue with their usual activities and manage their pain as normal (i.e., with analgesics).

**Outcome measures: Primary outcomes:** *Pain intensity.* Average pain intensity during the last 24 hours during menstruation will be assessed using the 0–10 NRS,^41^ with 0 representing ‘No pain’ and 10 representing ‘Worst imaginable pain’.

*Absenteeism from university*: Access to a prospective electronic diary will be provided for each participant to record university absenteeism. Electronic diaries are reported as highly acceptable and feasible to use.^44^ Significantly increased compliance and accuracy have been reported with e-diary recording compared with traditional paper diaries.^44^

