*Economic evaluation*. We will analyse the results of HIAT versus WLC over a 12-week, within-trial period (i.e., at T2).^28^ The cost-effectiveness for the entire 28-week time horizon will also be explored through T3 data observed in the HIAT arm and extrapolation of WLC data.^28^ The primary analysis will be conducted from a societal perspective (short-term direct costs, intervention costs, costs unrelated to the intervention [healthcare services and medication costs] and indirect costs, such as absence from work and impact on productivity due to primary dysmenorrhea).^48^ The secondary analysis will be conducted from a healthcare perspective (direct costs, including intervention costs and costs of other care, *excluding* absenteeism costs).^48^ Cost and absenteeism data that are collected at baseline (i.e., previous three menstrual cycles) will be used as predictors of future costs in the analysis. The EQ-5D-3L will be used to determine the QoL for the HIAT and WLC groups. The cost per participant will be calculated by multiplying unit costs identified from the HK government standardised national price list and resource quantities.^28^

An electronic diary (<https://forms.gle/gvoLHAoDqySQFr4GA>) will be used to record cost expenditures and work absenteeism. All participants will be provided with access to the cost diary, post-randomisation. Participants with limited access to the internet will be provided with printed hard copies of the cost and absenteeism diary, along with stamped and addressed return envelopes. Participants will be instructed to complete the diary during the week of menstruation each month. The research team members will be able to access the electronic diary to obtain a summary of the completed items for all study participants. The student assistant will contact participants by telephone for incomplete entries, to acquire additional details, or for failure to complete the diary.

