**Qualitative study (semi-structured focus groups):** The qualitative study will provide insight into the participants’ experiences during and attitudes towards the study intervention. During focus group discussions, attempts will be made to identify the subjective experiences with participation in HIAT and participants’ perceived improvements in menstrual pain, university attendance, and academic performance. For this component of the research, a computer-generated randomisation schedule will be generated and utilised to identify 70 participants (from the 130 participants included in the RCT), to participate in the focus groups. Ethics approval and written informed consent will be obtained before enrolment. A total of seven focus groups will be conducted at 32 weeks post-randomisation. Each group will consist of a random sample of 8-10 participants and will last between 30 and 45 minutes. Focus groups will be conducted in private rooms at PolyU. If the coronavirus disease 2019 pandemic continues, face-to-face seminars will be replaced with virtual meetings (Zoom) to allow appropriate social distancing. Two researchers, a moderator (PI) and a co-moderator (RPg student), will conduct the focus groups, and a third research team member will take notes. The interviews will be recorded using a digital voice recorder, in addition to taking notes. Semi-structured discussion guides will be used.

***Treatment fidelity and missed sessions.*** To optimise adherence to exercise sessions at PolyU, a student assistant will contact any participant who has missed an exercise session and attempt to re-schedule that session. Following the baseline assessment, all participants will be provided with information regarding how to access and complete the electronic diaries.

***Retention plan.*** To maximise retention we: (1) will obtain the contact information of participants and any friends and relatives who may know their whereabouts, and obtaining permission to follow-up the listed contact persons; (2) include appointments for data collection in the study schedule; (3) schedule supervised exercise at convenient times; and (4) offer a remuneration of HK$ 200 to cover the costs incurred during study participation.

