**Statistical tests and anticipated results**

*Missing data and data preparation*. We will implement strategies, such as the digital diary, follow-up phone-call reminders, and providing routine encouragement to continue exercise, to minimise missing data. Missing values will be replaced with group means. All statistical analyses will be performed on an intention-to-treat basis, using SPSS (version 24).

***Hypothesis 1.*** The two phases that each participant completes during the course of a cross-over trial are typically referred to as the two study periods.^49^ First, a preliminary test will be carried to rule out carryover effects and to test our study for validity.^50^ This will be performed by estimating the sum of the values measured during the two treatment periods for each participant and compared across the groups by using an independent samples *t*-test.^49^ Second, the within-participant differences in outcome variables between the study periods will be calculated using a two-sided Student’s unpaired *t*-test.^49, 50^ Treatment effects will be evaluated using an ANOVA with a mixed-effects model considering the longitudinal repeated measures, including the effects of time (T1, T2, and T3) within each study group and the interaction between time and intervention. Post hoc analysis using the Bonferroni correction will be performed. Hypothesis 1 will be supported if significant reductions in pain intensity and university absenteeism and a significant improvement in academic performance are reported following 12 weeks of HIAT compared with baseline measurements.

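### University absenteeism has no scheduled-class denominator and an apparently retrospective baseline, so the change-from-baseline rule of Hypothesis 1 can show or hide an effect for reasons unrelated to HIAT

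*Protocol*

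**What the plan says.** - **Outcome.** Under Primary outcomes, absenteeism from university is described by its instrument only: "Access to a prospective electronic diary will be provided for each participant to record university absenteeism". No unit, counting window, attribution to menstrual pain or number of scheduled classes is given. Nothing in the protocol mentions term dates, holidays or examination periods, although the last outcome assessment (T3) is at 28 weeks.
- **Baseline.** Under Procedure, the in-person session before randomisation includes "Baseline assessments of primary and secondary outcomes and the costs and absenteeism data associated with each" woman's previous three cycles. The Economic evaluation section confirms the window: "absenteeism data that are collected at baseline (i.e., previous three menstrual cycles".
- **Start of diary recording.** Under Treatment fidelity and missed sessions: "Following the baseline assessment, all participants will be provided with information regarding how to access and complete the electronic diaries". The Economic evaluation section says of the cost diary: "All participants will be provided with access to the cost diary, post-randomisation", and adds: "Participants will be instructed to complete the diary during the week of menstruation each month". That section describes its diary as covering costs and work absence. Whether it is the same diary as the one for university absenteeism is not stated.
- **Success rule.** Under Statistical tests, Hypothesis 1 is supported if pain, absenteeism and academic performance all show significant improvements that "are reported following 12 weeks of HIAT compared with baseline measurements". The same paragraph also plans an unpaired t-test on within-participant period differences and a time-by-intervention term, but the success rule refers to neither.

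**The concern.** A count of absences depends on how many classes there were to miss. A menses that falls on a weekend or in a break gives zero absence whatever the pain. Comparing two counts is fair only if the opportunity to be absent was similar in both windows, and the protocol collects nothing that would show this.

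The two sides of the comparison also seem to be recorded differently: looking back over three cycles at baseline, and in a prospective diary afterwards. Unlike breaks, which rolling entry may spread out, this change of method applies to every participant.

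Randomisation balances both influences between the arms. It does not balance them between before and after within an arm, and that is the comparison the success rule uses. A primary outcome could therefore appear to fall without any treatment effect, or a real fall could be hidden.

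**Working it through.** The protocol gives no absence rate, standard deviation or effect size for absenteeism, so there is no stated figure to reproduce. The check has three parts. All numerical inputs other than the sample size, cycle length and follow-up length are assumptions.

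**1. Effect of class days on a raw count.** Assume a constant absence rate per scheduled class day and a 12-week window with 5 class days a week (60 days). With *b* weeks of break in the window, the raw count changes by (60 − 5*b*)/60 − 1:

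- *b* = 1: −8%
- *b* = 2: −17%
- *b* = 4: −33%

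The rate per scheduled class day changes by 0% in each case. If only menstrual weeks are recorded, one of three menses falling in a break gives −33%.

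**2. Before-after test with no treatment effect.** Inputs: 43 women (the per-group number under Sample size for Hypothesis 1); mean μ of 1.5, 3 or 4.5 missed days per three-cycle window; person-level rates gamma with shape 1; Poisson counts; one-sample t-test on the change at two-sided 5%. If a fraction *c* of class days is lost at follow-up only:

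- mean change = −*c*μ
- variance = μ(2 − *c*) + *c*²μ²
- rate of false reductions ≈ Φ(*c*μ/SE − 2.018), with SE = √(variance/43)

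For μ = 3 and *c* = 1/6: mean −0.50, variance 5.50 + 0.25 = 5.75, SE = √(5.75/43) = 0.366, ratio 1.367, so Φ(−0.651) ≈ 0.26. Simulation with 20,000 replicates agrees:

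| Scenario, no treatment effect | μ = 1.5 | μ = 3 | μ = 4.5 |
|---|---|---|---|
| No break, no recall error | about 2.5% | about 2.5% | about 2.5% |
| Each cycle equally likely (1/6 or 1/3) to fall in a break, both windows | about 2.5% | about 2.5% | about 2.5% |
| One sixth of class days lost at follow-up only | 15% | 26% | 37% |
| No break, recall overstates baseline by 20% | 17% | 31% | 43% |

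The entries are significant reductions; the nominal rate in that direction is 2.5%. If the sixth is lost in the baseline window instead, the picture reverses: significant false increases appear in about 15%, 27% and 36% of trials, and false reductions almost vanish.

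**3. Concurrent randomised contrast.** A comparison of change between concurrent arms, with 45 or 65 women per arm, means of 1.5 and 3, gamma shape 2, and breaks and recall error applied alike to both arms, rejects in 4.5% to 5.4% of runs at the two-sided 5% level in every scenario. The bias disappears there. The variation from uneven class days remains.

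**The case against.** **The size rests on a one-sided assumption.** This stands. The 15% to 37% range needs every woman to lose class days at follow-up and none at baseline. Women enter individually on the first day of a menses, and training is supervised one to one, so simultaneous entry of a whole arm is unlikely. With breaks spread equally over both windows the error rate is nominal. A reader might infer that the calendar will favour HIAT, or that any of these rates is the trial's actual false-positive rate. The documents support neither. A weekend menses is noise, not bias. Balanced breaks would not, however, remove the change of recording method.

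**Hypothesis 1 needs three improvements.** This also stands. A reader might infer that a spurious fall in absenteeism could make the hypothesis succeed. It could not, because pain and academic performance must improve as well.

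**The baseline source is inferred.** This stands in part. Procedure lists baseline outcome assessments and the three-cycle data side by side, and the Economic evaluation uses the latter to predict costs. No other baseline for absenteeism is described, however, and diary instructions come afterwards, so a retrospective baseline is the natural reading, not a certainty.

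**The denominator is a diary-form or SAP detail.** This does not carry. The linked form is not shown and may ask about classes, but the protocol does not say so. If scheduled hours are not captured at the time, no later analysis plan can recover them reliably.

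**A diary baseline in the first menses looks like the obvious remedy.** It is a poor trade. At a mean of 3 per three cycles (1 per cycle), the variance of the per-cycle change is 1/3 + 1/3 = 0.67 with a three-cycle baseline (SD 0.82) and 1 + 1/3 = 1.33 with a single menses (SD 1.16), which is double. Baseline assessment is on day 1 with randomisation next, so the rest of that menses would be recorded after allocation. Three cycles of 24 to 30 days (72 to 90 days) also match the 84-day follow-up well.

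**Conclusion.** The point holds as a fault in how one primary outcome is measured and judged. It lacks a denominator, its baseline and follow-up are apparently recorded by different methods, and the stated success rule compares across both differences without the protection of randomisation. The resulting error can go either way.

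The size cannot be derived from the documents, which give no absence rates, term dates or recruitment calendar. Under the stated model it runs from nominal (breaks equal in both windows) to 15% to 37% false reductions (one sixth of class days lost at follow-up only). A 20% overstatement at baseline has an effect of similar order.

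The consequence is a false claim for absenteeism as a single outcome, or a blocked Hypothesis 1 when a real effect is hidden. It does not extend to a biased HIAT versus wait-list comparison: there the two influences cancel in expectation, and the loss is precision. The change should be made before data collection, because the missing information cannot be rebuilt later.

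**What to change.** 1. Add a diary item for scheduled class hours (or days) on each menstrual day.
2. Define the outcome as hours missed because of dysmenorrhoea divided by hours scheduled. Treat a menses with no scheduled classes as not applicable: neither zero nor filled with the group mean, which the missing-data paragraph would otherwise imply.
3. Keep the three-cycle baseline, ask the same missed and scheduled items in it, and use it as a covariate.
4. Draw the absenteeism conclusion from the diary-recorded HIAT versus wait-list contrast that the Hypothesis 1 analysis already plans, not from a retrospective baseline set against a diary.

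The cost is one extra diary item, the matching questions at baseline and a reworded success rule for this outcome. No visit is added. The downside is that some woman-cycles will contribute no absenteeism data.
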